## Abstract

**Background:**

Periodontal disease is the most common oral disease affecting adults, and although it is largely preventable it remains the major cause of poor oral health worldwide. Accumulation of microbial dental plaque is the primary aetiological factor for both periodontal disease and caries. Effective self-care (tooth brushing and interdental aids) for plaque control and removal of risk factors such as calculus, which can only be removed by periodontal instrumentation (PI), are considered necessary to prevent and treat periodontal disease thereby maintaining periodontal health. Despite evidence of an association between sustained, good oral hygiene and a low incidence of periodontal disease and caries in adults there is a lack of strong and reliable evidence to inform clinicians of the relative effectiveness (if any) of different types of Oral Hygiene Advice (OHA). The evidence to inform clinicians of the effectiveness and optimal frequency of PI is also mixed. There is therefore an urgent need to assess the relative effectiveness of OHA and PI in a robust, sufficiently powered randomised controlled trial (RCT) in primary dental care.

**Methods/Design:**

This is a 5 year multi-centre, randomised, open trial with blinded outcome evaluation based in dental primary care in Scotland and the North East of England. Practitioners will recruit 1860 adult patients, with periodontal health, gingivitis or moderate periodontitis (Basic Periodontal Examination Score 0–3). Dental practices will be cluster randomised to provide routine OHA or Personalised OHA. To test the effects of PI each individual patient participant will be randomised to one of three groups: no PI, 6 monthly PI (current practice), or 12 monthly PI.

Baseline measures and outcome data (during a three year follow-up) will be assessed through clinical examination, patient questionnaires and NHS databases.

The primary outcome measures at 3 year follow up are gingival inflammation/bleeding on probing at the gingival margin; oral hygiene self-efficacy and net benefits.

**Discussion:**

IQuaD will provide evidence for the most clinically-effective and cost-effective approach to managing periodontal disease in dentate adults in Primary Care. This will support general dental practitioners and patients in treatment decision making.

**Trial registration:**

Protocol ID: ISRCTN56465715

## Background

Periodontal disease is the most common oral disease affecting adults. This disease is largely preventable, yet it remains the major cause of poor oral health worldwide and is the primary cause of tooth loss in older adults [1]. Accumulation of microbial dental plaque is the primary aetiological factor for both periodontal disease and caries. Susceptibility to periodontal disease is also influenced by the host’s defence mechanisms to bacterial infection and other risk factors such as calculus and smoking [2]. Periodontal disease affects tissues surrounding and supporting the teeth and is classified into two broad categories: gingivitis and periodontitis. Gingivitis is a reversible condition characterised by inflammation and bleeding at the gingival margin. It is a pre-requisite for periodontitis and is also a risk indicator for caries progression [3]. Periodontitis is the irreversible destruction and loss of the supporting periodontal structures (periodontal ligament, cementum and alveolar bone) [2]. The result is unsightly gingival recession, sensitivity of the exposed root surface, root caries (decay), mobility and drifting of teeth and, ultimately, tooth loss.

Effective self-care (tooth brushing and interdental aids) for plaque control and removal of risk factors such as calculus, which can only be removed by periodontal instrumentation (PI), are considered necessary to prevent and treat periodontal disease thereby maintaining periodontal health.

The 1998 UK Adult Dental Health Survey (ADHS) provides some evidence that the majority of UK adults might be at risk of developing periodontal disease: 72% of dentate adults had visible plaque, indicating tooth brushing was ineffective, and 73% had calculus on at least one tooth [4]. Forty-three percent of adults had some moderate periodontal disease (at least one periodontal pocket with a probing depth of ≥ 4 mm < 6 mm) increasing by age from 14% aged 16–24 to 85% ≥65. Indicators of severe disease (periodontal pocket depth ≥ 6 mm) also increased with age affecting 31% of ≥65 year olds [4]. A recent study of adults aged 20 to 55 in Scotland provided evidence that the 1998 ADHS figures underestimate the current extent of periodontal disease. Only 15% exhibited no clinical signs of disease and 63% exhibited moderate disease [5].

Despite evidence of an association between sustained, good oral hygiene and a low incidence of periodontal disease and caries in adults [5] there is a lack of strong and reliable evidence to inform clinicians of the relative effectiveness (if any) of different types of Oral Hygiene Advice [6] (OHA).

A number of relevant systematic reviews evaluating OHA have been conducted with some inconsistency in their findings [7-9]. The most recent, a Cochrane review of psychological interventions to improve adherence to oral hygiene instruction in adults with periodontal disease found evidence that psychological interventions resulted in improvements in oral hygiene related behaviours and self-efficacy beliefs [7]. However, only four low quality trials were eligible for inclusion and the authors concluded there was a need for greater methodological rigour in trials in this area. A review of studies reporting clinical health outcomes concluded that most OHA interventions provide a short-term (≤ 6 month) reduction in plaque and gingival bleeding [6]. The authors highlighted the lack of and need for studies to assess the sustainability of these short-term benefits.

The evidence to inform clinicians of the effectiveness and optimal frequency of PI is mixed. The West Midlands Health Technology Assessment Group’s systematic review of PI (including root planing) for chronic periodontal disease in specialist settings concluded that the quality of the research base, in terms of study design, quality of reporting and statistical reporting, was poor. Some positive effects (reduction in pocket depth and bleeding on probing) were found, but the marginal effect of quarterly PI over annual PI was small. No long term studies where annual PI was carried out were identified; no studies investigated patient centred outcomes; and the authors highlighted the need for further research to determine the generalisability of the findings to general dental practice [10]. The Cochrane systematic review of PI (i.e. single-visit periodontal instrumentation without root planing) for adults found the evidence for effectiveness and optimal frequency to be weak and unreliable, providing little guidance for policy makers, dental professionals or patients [11]. Only nine trials were eligible for inclusion, all had a high risk of bias and it was not possible to carry out a meta-analysis. Given that PI is routinely provided in general dental practice it is noteworthy that none of the eligible trials were conducted in primary care, included patient centred outcomes, economic analyses or long term effects. Evidence from a recent systematic review suggests that stability of clinical attachment for patients with a history of chronic periodontitis receiving supportive periodontal care (non-surgical and surgical) is greater, but less cost-effective, in specialist settings than in general practice settings. However, this conclusion was based on only three studies and the estimates of cost-effectiveness used data from only one study. The need for further research, including research investigating patients’ willingness to pay, was highlighted [12].

There is therefore an urgent need to assess the relative effectiveness of OHA and PI in a robust, sufficiently powered randomised controlled trial (RCT) in primary dental care.

### Trial aim

The aim of this study is to compare the effectiveness and cost-effectiveness of theoretically based, personalised oral hygiene advice (OHA) or periodontal instrumentation (PI) at different time intervals (no PI; 6 monthly PI or 12 monthly PI) or their combination, for improving periodontal health in dentate adults attending general dental practice.

### Objectives

The primary objectives are to test the effectiveness and cost effectiveness of the following dental management strategies:

a) Personalised OHA versus routine OHA;

b) 12 monthly PI versus 6 monthly PI;

c) No PI versus 6 monthly PI.

The secondary objectives include:

d) To test the effectiveness and cost-effectiveness of a combination of personalised OHA with different time intervals for PI;

e) To measure dentist/hygienist beliefs relating to giving OHA, PI and maintenance of periodontal health.

## Methods/Design

This is a 5 year multi-centre, randomised, open trial with blinded outcome evaluation. The comparisons will be made within a factorial design using a combination of cluster and individual participant randomisation. As personalised OHA will be given by the dentist or hygienist, there is a theoretical risk of “contamination” between patient participants seen within the same dental practice (i.e. the dentist will give personalised OHA to participants allocated to routine care). To minimise this potential risk, dentists will be randomised to either a routine or a personalised OHA group. All patient participants seen by the same dentist or hygienist (a “cluster”) will receive either routine (current practice) or personalised OHA depending on their dentist’s allocation. To test the effects of PI each individual patient participant will be randomised to one of three groups: no PI, 6 monthly PI (current practice), or 12 monthly PI Figure 1.

**Figure 1 F1:**
[figure not shown]
Study design.

### Trial interventions

In general dental practice both OHA and PI can be delivered by a dentist or by a dental hygienist. The trial will recruit dentists however the interventions will be delivered by the dentist or by the hygienist in line with each individual dentist’s usual practice.

#### **
*Routine OHA*
**

Routine OHA indicates current practice. There is no published information describing “routine” OHA, but anecdotal evidence suggests that this is often the provision of minimal advice (e.g. “you need to brush your teeth more frequently” or no advice).

#### **
*Personalised OHA*
**

The content and delivery of the intervention is summarised as a series of steps in Figure 2. We will use a personalised OHA intervention based upon Social Cognitive Theory [13] and Implementation Intention Theory [14]. The content of the advice delivered will be personalised according to the dentist’s/hygienist’s assessment of the needs of the patient. At a minimum the content will include advice and instruction in self diagnosis (e.g. bleeding gums on brushing indicates the presence of reversible gingival inflammation) and advice and instruction on tooth brushing and flossing (frequency and technique). Upon completion of the advice, the dentist will agree an action plan with the patient. The feasibility and utility of including personalised biofeedback [15] in the personalised OHA intervention will be considered by the research team and the Periodontal Advisory Group.

**Figure 2 F2:**
[figure not shown]
The OHA intervention behavioural framework.

#### **
*Dentist allocation to OHA group*
**

Recruited dentists will be allocated to routine or personalised OHA by minimisation on two factors - (i) practice employs dental hygienist (yes/no) and (ii) practice size (2 or less dentists in practice/3 or more dentists). This cluster level randomisation will be conducted after the dental consent form is received at the Trial Coordinating Office in Dundee (TCOD) and before any patient has been approached.

#### **
*Training in delivery of the personalised OHA*
**

Training in the delivery of the personalised OHA intervention will be provided to all dentists/hygienists allocated to this OHA group. Training will provided at half day training sessions and, in addition, interactive DVDs which include training and self-assessment elements will be provided. Dentists/hygienists will retain these training resources in order to be able to undertake self-directed training as required throughout the trial.

#### **
*Frequency of OHA*
**

At baseline all patients will receive OHA according to cluster level randomisation. Reinforcement of OHA will be provided at the discretion of the dentist/hygienist during the trial and recorded.

#### **
*Periodontal Instrumentation (PI)*
**

The definition of periodontal instrumentation is as used in standard practice and may include the removal of plaque and calculus from the crown and root surfaces using manual or ultrasonic scalers, with no adjunctive sub-gingival therapy e.g. antibiotics [17], and the appropriate management of plaque retention factors.

#### **
*Baseline PI*
**

A full mouth supra and sub-gingival PI will be carried out by the dentist/hygienist on all participants prior to randomisation. No time limit will be set on this treatment and dentists/hygienists will be instructed to scale the teeth and root surfaces until they are free of all deposits and are smooth to probing.

#### **
*Experimental PI*
**

Experimental groups will receive a PI at six or 12 monthly intervals according to the individual patient-level randomisation. Participants allocated to the no PI groups will attend their dentist at time intervals which are determined by current practice. However, if a patient allocated to the no PI group does not attend their dentist for an appointment within 12 months the dentist will be asked to call them in for an appointment.

#### **
*Patient participant allocation to PI group*
**

Patient participants’ allocation to the PI trial arms will use the automated, central randomisation service at the Centre for Healthcare Randomised Trials (CHaRT), University of Aberdeen, with access both by telephone and web. Allocation will take place once the outcome assessor has completed the baseline outcome assessment and will be minimised on (i) absence of gingival bleeding on probing (yes/no), (ii) highest sextant BPE score (BPE less than 3/BPE 3) and (iii) current smoking (yes/no). The outcome assessors will be informed that allocation has taken place. However, the actual allocation will be transmitted to the TCOD (thereby keeping the outcome assessors blinded to allocation). A letter will be sent to patient participants to inform them of their trial group allocation and the practice will be contacted by the TCOD to arrange the first intervention appointment. The patient participant’s trial group allocation and date of first PI intervention appointment will be entered into an automated reminder system. For participants allocated to the “no PI” groups no PI intervention appointments will be made and these participants will attend their dentist as per current practice. However, the TCOD will arrange a routine check-up appointment for patients allocated to these groups who do not attend their dentist at least once in every 12 month period.

### Study recruitment and allocation

#### **
*Study recruitment - identifying and recruiting dentists*
**

We propose to utilise existing collaborative links with Practitioner Services Division Scotland (PSD), and the NHS Business Services Authority England/Wales (NHSBSA). Each of these agencies maintains a database detailing all courses of NHS treatment provided. Agreement will be sought to use these databases, with the appropriate data protection safeguards in place, to identify all potentially eligible dentists. The information identifying dentists is publicly available from each Health Board/Primary Care Trust. The databases we propose to use collate this information making identification more efficient.

The Trial Co-ordinating Office in Dundee (TCOD) will send potential dentist participants an invitation letter, describing the study and the dentist will be phoned to confirm their attendance to the recruitment session. Dentists who indicate they would like to be contacted about the trial will be invited to a local information and recruitment session.

#### **
*Identifying and recruiting patients*
**

The identification of potential patients in each dental practice will be supported by staff from the Scottish Primary Care Research Network in Scotland and the UK Clinical Research Network in England. Dentists will identify the patients” addresses and will then send the patient invitation letter, information sheet and baseline patient questionnaire to each potential participant with an appointment to attend a screening session in the dental practice. This will be sent at most six weeks in advance. At this stage patients who are not interested in taking part will be asked to phone the practice to be sent an alternative appointment to see their dentist. At the screening appointment the dentist will discuss the trial with the potential participants and answer any questions. The outcome assessor, who will be a qualified hygienist employed on the trial, will be present at this appointment. Those who state they do not wish to take part will then be seen by their dentist/hygienist who will provide OHA and/or PI as normal. Eligibility of those who express an interest in taking part will be checked by the outcome assessor and confirmed against pre-defined criteria. Those who are eligible will be consented to the trial by the outcome assessor. Baseline questionnaires will then be collected and baseline clinical outcomes will be measured by the outcome assessor before the dentist/hygienist provides the baseline PI. For those patients excluded from the trial solely on BPE score 4 or *, consent will be sought to follow them up with the annual questionnaire.

### Inclusion criteria

Adult patients (≥ 18 years of age) with periodontal health, gingivitis or moderate periodontitis (Basic Periodontal Examination (BPE) score 0–3) who:

• Are dentate.

• Have attended for a check-up at least twice in the previous 2 years.

• Receive their dental care in part or fully as an NHS patient.

### Exclusion criteria

• Patients with periodontal disease with a BPE score of 4 (probing depth > 6 mm and/or furcation involvements or attachment loss of 7 mm or more) in any sextant on the basis more extensive periodontal care is indicated.

• Patients with an uncontrolled chronic medical condition (e.g. diabetes, immunocompromised).

### Outcome measures

#### **
*Primary outcomes*
**

*****Clinical*****: gingival inflammation/bleeding on probing at the gingival margin at 3 year follow-up;

*****Patient Centred*****: oral hygiene self-efficacy at 3 year follow-up;

*****Economic*****: Net benefits (mean willingness to pay minus mean costs).

#### **
*Secondary outcomes*
**

*****Clinical*****: 1) calculus, 2) periodontal pocket depth, 3) additional PI, 4) referral (all at 3 year follow-up)

*****Patient Centred*****: 1), dental quality of life, 2) oral health behaviour, 3) knowledge; (annual follow-up to 3 years)

*****Economic******:* Costs to the NHS and patients; willingness to pay

*****Providers*****: Beliefs relating to giving oral hygiene advice and maintenance of periodontal health.

Note: The Periodontal Advisory Group considers that clinical attachment loss (CAL) and plaque cannot be measured reliably and so neither are included as outcomes.

### Data collection and processing

Participating dental practices will be expected to maintain a file of essential trial documentation which will be provided by the TCOD.

### Collection of clinical outcome measures

Clinical outcomes will be measured at baseline and at three years follow-up by trained outcome assessors who are blinded to allocation. Gingival inflammation as bleeding will be measured according to the Gingival Index of Löe [16] by running a University of North Carolina (UNC) probe circumferentially around each tooth just within the gingival sulcus or pocket. After 30 seconds, bleeding will be recorded as being present or absent on the buccal and lingual surfaces. The colour-coded UNC periodontal probe will be used to measure periodontal pocket depth and presence of calculus. Clinical outcomes will be measured for all teeth (excluding third molars) at 6 sites per tooth [mesiobuccal, midbuccal, distobuccal, mesiolingual/palatal, mid-lingual/palatal and distolingual/palatal]. The sequence of scoring will be gingival inflammation/bleeding, periodontal pocket depths and calculus.

Additional PI and referral will be measured annually by self-administered patient questionnaire and at three years from routinely collected data.

### Collection of patient centred outcome measures

Patient centred outcomes will be measured at baseline and annually by self-administered postal questionnaire. Quality of life will be measured using the Oral Health Impact Profile-14 (OHIP-14) [17]. Issues of cosmesis will be explored. The questions for measuring patient and provider beliefs are derived from Social Cognitive Theory [13] and the Theory of Planned Behaviour [18].

For patient participants who fail to attend their year three assessment appointments all efforts will be made to collect clinical outcome data and questionnaires will be posted.

### Collection of economic measures

Time, travel and treatment costs associated with all visits to the dentists/hygienists will be collected by questionnaires administered to patients at the baseline visit. Questionnaires recording the costs of any treatment provided will be completed by the dentist/hygienist. Contact with other health services will be assessed via the annual patient questionnaire.

Benefits to patients of the various interventions will be measured over a number of dimensions. The effectiveness of the intervention will be measured by the outcomes listed above. Public preferences will be elicited regarding the relative importance of these outcomes from a discrete choice experiment (DCE) (see economic analysis. The DCE will be administered to a separate sample of the public obtained from an online marketing company over the course of the trial.

### Scheduling of events

Data will be collected as detailed in Table 1.

**Table 1 T1:** Scheduling of events

	**Screening**	**Baseline**	**12 months**	**24 months**	**36 months**
Assessment for eligibility	**X**				
Informed consent	**X**				
Gingival bleeding		**X**			**X**
BPE score		**X**			**X**
Calculus		**X**			**X**
Pocket depth		**X**			**X**
QoL questionnaire (OHIP-14)		**X**	**X**	**X**	**X**
Knowledge, attitudes, beliefs questionnaire		**X**	**X**	**X**	**X**
Costs questionnaire		**X**			**X**
Clinician belief questionnaire		**X**			**X**

## Analysis plan

### Statistical analyses

The factorial design of the trial allows for the main effects and interactions between interventions to be examined. Reflecting the clustering in the data, the outcomes will be compared using multilevel models, with adjustment for minimisation variables [19]. Statistical significance will be at the 2.5% level and corresponding confidence intervals will be derived. All participants will remain in their allocated group for analysis (intention to treat). Subgroup analyses using interaction terms will explore the possible effect modification of a number of factors (See Sub group analysis), all using stricter levels of statistical significance (p < 0.01). Missing patient reported outcomes will not be imputed at the follow-up time points for the primary analyses. However, we will investigate the mechanism of missingness using regression models [20] and apply an appropriate missing data model as a sensitivity analysis [21]. All trial analyses will be according to a statistical analysis plan that will be agreed in advance by the Trial Steering Committee (TSC). The Data Monitoring and Ethics Committee (DMEC) will meet at 9, 24 and 36 months to review progress and recommend any divergences from planned trial design.

A single main analysis will be performed at the end of the trial when all follow-up has been completed. Unblinded interim analyses will be conducted for the DMEC meetings as required.

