### Sample size

An OHA exploratory trial in the same population as the proposed trial demonstrated that at baseline 35% of gingival sites were bleeding on probing with sd = 25% [27]. The PI Cochrane review suggested that a reduction of 15% of sites with bleeding was a plausible reduction for 6 monthly PI [12]. If the effect is assumed linear, halving the number of PIs should half the expected difference of 15% of sites. If the effect is non linear and larger than 7.5%, the trial will be adequately powered. If the effect is smaller it would be of questionable clinical significance. There is some evidence that personalised OHA can reduce the number of gingival sites bleeding on probing by approximately 7.5% [27]. The following calculations are based on estimating main effects from the trial. All calculations assume a significance level of 2.5% to give some protection against multiple testing.

#### **
*OHA*
**

To calculate the sample size required to estimate the main effect of OHA, it is recognised that the data are contained within a cluster RCT. Assuming a conservative estimate of the intracluster correlation (ICC) of 0.0531, a cluster RCT of 50 dentists collecting information from 25 patient participants each (25*25 = 625 patients per arm) will have 90% power to detect a difference of 7.5%. Should the correlation be 0.1, the trial will still have approximately 80% power to detect a difference of 7.5%.

#### **
*PI*
**

Given that the comparison of routine versus personalised OHA requires 625 patient participants in each arm, equal randomisation 1:1:1 (no PI; 6 monthly; 12 monthly) of patient participants implies 208 in each of the six groups. Assuming no interaction effect, the corresponding PI groups can be combined across both routine and personalised advice groups giving 416 patients allocated to each PI group. Assuming a sample size of 416 in each group, the trial will have in excess of 95% power for each pairwise comparison to detect a difference of 7.5% in the percentage of gingival sites that bleed on probing.

#### **
*Interaction*
**

We do not anticipate a substantive interaction effect between the PI interventions and the personalised OHA. Assuming an ICC of 0.05, the trial has 80% power to detect an interaction effect of 7.5%. Should the ICC be 0.1, the trial has approximately 80% power to detect an interaction of 10%.

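### The stated model adjusts only for minimisation variables; adding each outcome's own baseline value would give more precision without new data

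*Protocol article*

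**What the plan says.** Statistical analyses gives the model for the outcomes: "the outcomes will be compared using multilevel models, with adjustment for minimisation variables". The variables meant are listed in two places.

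- **Patient level** (Patient participant allocation to PI group): allocation is "minimised on (i) absence of gingival bleeding on probing (yes/no"), with highest BPE score below 3 or equal to 3, and current smoking.
- **Dentist level** (Dentist allocation to OHA group): "Recruited dentists will be allocated to routine or personalised OHA by minimisation on two factors", namely whether the practice employs a hygienist and practice size.

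No section names the baseline value of an outcome as a covariate, and the sample size uses the raw SD with no allowance for baseline.

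The baseline values are collected. "Clinical outcomes will be measured at baseline and at three years follow-up by trained outcome assessors who are blinded to allocation", and "bleeding will be recorded as being present or absent on the buccal and lingual surfaces", so each patient has a percentage of bleeding sites before PI allocation. The section on patient-centred outcomes has these measured by questionnaire at baseline and annually, and Table 1 agrees.

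**The concern.** The primary clinical outcome is the extent of bleeding. The covariate set keeps only whether there was any bleeding at baseline. Sample size reports that "at baseline 35% of gingival sites were bleeding on probing", with an SD of 25%, so most of the spread lies among patients who bleed somewhere, and a yes/no split cannot separate them. BPE and smoking may recover part of this, but neither measures how many sites bleed. For self-efficacy, no minimisation variable is a baseline measure of the outcome.

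Two things are at stake. The first is precision, chiefly for the OHA comparison, where clustering costs most. The second is protection against baseline differences between OHA arms. Dentists are allocated before any patient is approached, and the allocated dentist then sends the invitations and discusses the trial. Arms could differ at baseline by chance among 50 to 60 dentists or through differential recruitment. A yes/no indicator corrects such differences only coarsely.

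**Working it through.** **Inputs from Sample size.** Difference 7.5 points, SD 25, significance level 2.5% (taken as two-sided, z = 2.241), 25 dentists per arm with 25 patients each (625 per arm), ICC 0.05 or 0.1, 416 patients per PI group.

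**Step 1: the plan's own figures (no covariates).** SE = 25 × √(2 × DE / 625), with DE = 1 + 24 × ICC; power = Φ(7.5/SE − 2.241).

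- OHA, ICC 0.05: DE = 2.2, SE = 2.098, power 90.9%. The stated 90% reproduces. (At the printed 0.0531, power is 89.9%.)
- OHA, ICC 0.1: DE = 3.4, SE = 2.608, power 73.7%. The protocol says approximately 80%; 82.0% appears only at a two-sided 5% level.
- PI pairs: SE = 25 × √(2/416) = 1.733, power 98.1%, consistent with the stated figure of more than 95%.

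**Step 2: how much baseline information any/none carries.** Let p0 be the share of patients with no bleeding sites. The indicator explains R = p0(1 − p0)(35/(1 − p0))² / 25² = 1.96 × p0/(1 − p0) of the baseline variance.

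- p0 = 5%: R = 0.103.
- p0 = 15%: R = 0.346.

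p0 is not given. An assumed beta-binomial with mean 35% and SD 25% puts it at 1.5% (156 sites) to 4.1% (52 sites). The Background cites a Scottish sample aged 20 to 55 in which 15% had no clinical signs of disease. I use 5-15%, which gives any/none bleeding more credit than the beta-binomial would.

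**Step 3: residual variance.** r is not in the documents; I assume 0.3 and 0.5. If the outcome depends linearly on the baseline percentage, the variance is multiplied by 1 − r²R with any/none in the model, and by 1 − r² with the continuous value. BPE and smoking are not credited in either model.

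**Step 4a: OHA power, baseline explaining variance at both levels.** SE is multiplied by the square root of the factor. Example (ICC 0.1, r = 0.5, p0 = 5%):

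- Any/none: 2.608 × √0.974 = 2.574, so Φ(2.914 − 2.241) = 74.9%.
- Continuous: 2.608 × √0.75 = 2.258, so Φ(3.321 − 2.241) = 86.0%.

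| r | p0 | ICC 0.05: any/none → continuous | ICC 0.1: any/none → continuous |
|---|---|---|---|
| 0.3 | 5% | 91.2% → 93.4% | 74.2% → 78.0% |
| 0.3 | 15% | 91.8% → 93.4% | 75.2% → 78.0% |
| 0.5 | 5% | 91.6% → 97.0% | 74.9% → 86.0% |
| 0.5 | 15% | 93.3% → 97.0% | 77.9% → 86.0% |

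**Step 4b: OHA power, baseline explaining within-dentist variance only.** SE² = 2 × 625 × [ICC/25 + (1 − ICC) × factor/625]. Example (ICC 0.1, r = 0.5, continuous): 1250 × (0.00400 + 0.00108) = 6.35, SE = 2.520, power 76.9%.

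| r | p0 | ICC 0.1: any/none → continuous |
|---|---|---|
| 0.3 | 5% | 73.8% → 74.8% |
| 0.3 | 15% | 74.1% → 74.8% |
| 0.5 | 5% | 74.0% → 76.9% |
| 0.5 | 15% | 74.8% → 76.9% |

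The gain here is about 1-3 points.

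**Step 5: PI pairs.** Power moves from 98.2-98.9% (any/none) to 98.9-99.7%. The useful effect is on interval width, which is multiplied by √((1 − r²)/(1 − r²R)). This runs from 0.97 (r = 0.3, p0 = 15%) to 0.88 (r = 0.5, p0 = 5%), so intervals are about 3-12% narrower.

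**Self-efficacy.** The protocol gives no SD, target difference or correlation for it, so no size is calculated. The reasoning is the same, except that the planned model holds no version of its baseline at all.

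**The case against.** The strongest reply is that nothing here is wrong. Adjusting for minimisation variables is a valid analysis. The sentence does not say that no other covariate will be used, and the same section defers to a statistical analysis plan agreed in advance, which is not at hand and may add baseline. That stands in part: a reader might infer that the protocol rules out baseline adjustment or that its analysis is biased, and the text supports neither. But the article does not leave the covariates open. It names a set, and that set is weaker than the data collected allow.

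The reply on size also has force. Measured from a model with no covariates, OHA power at ICC 0.1 would seem to rise from 74% to 78%, 86% or 91% at r = 0.3, 0.5 or 0.6. That overstates the gain, because the planned model already includes any/none bleeding, BPE and smoking, and because the correlation is assumed to act between dentists as well as within them. Moreover, everyone receives a full-mouth PI after the baseline measurement, and three years follow, so r may be low. At the planning ICC of 0.05, OHA power is already about 91%, so there is no power shortfall to repair there or for PI.

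A reader might also want region (Scotland or North East England) as a covariate, since it is not a minimisation factor. The documents do not support this: they give no effect of region on the outcome, and the Discussion mentions payment systems as one of several varied circumstances without assigning them to regions.

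**Conclusion.** The point holds as an improvement in efficiency and robustness, not as an error in the analysis. For the OHA comparison at ICC 0.1, the gain over a model with any/none bleeding runs from about 1 to 11 points of power, according to r (0.3-0.5 assumed), the share of patients with no bleeding (5-15% assumed) and whether baseline explains between-dentist variance. At ICC 0.05, with both levels explained, it is about 2-5 points. For PI the benefit is narrower intervals. BPE and smoking are not credited, so the true increment could be somewhat smaller. For the OHA arms, adjustment for the continuous value also deals more directly with differences in measured baseline bleeding; it cannot correct for unmeasured differences in who was recruited.

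**What to change.** Under Statistical analyses, change the model sentence to: *multilevel models adjusted for the baseline value of the outcome (percentage of bleeding sites as a continuous covariate; baseline self-efficacy score for the patient-centred outcome) and the minimisation variables*. Carry the same wording into the statistical analysis plan, and fix it before unblinding so that it is not a post hoc choice.

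The cost is a change of wording, one extra parameter per model, and a simple rule, stated in advance, for any missing baseline values. No new data are needed. No region covariate is proposed.
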